#### **5.6.8.2 Renal Toxicity**

Urinalysis (as described in Section 5.6.5.9) will be conducted every 2 weeks during the treatment part of each 12 week cycle. In addition, 24-hour urinalysis will be conducted if any of the criteria described in Section 5.6.5.9 are met on two consecutive weekly samples.

If a subject meets any of the following criteria, study medication will be stopped until such time that the Sponsor (in discussions with the Investigator) considers that the benefit of further treatment with PRO051 outweighs the risk to the individual subject. Given the progressive and fatal nature of this disease, it is important that the renal stopping criteria allow the flexibility for the potential to re-start dosing in this population following an individual subject benefit: risk assessment.

- Proteinuria in 24-hour urine sample is either >300 mg/day or 8 mg/m^2/h (whichever is reached first); or
- Albumin excretion in 24-hour urine sample is >50 mg/day; or
- New appearance of casts (other than hyaline casts up to 200/mL) or erythrocytes (≥5 cells/hpf). An additional fresh spot urine sample will be required for this analysis

Routine non-invasive renal imaging will not be performed for subjects participating in the study. However, if a subject experiences persistent and progressive renal impairment, further investigations which may include non-invasive imaging and renal biopsy will be considered on an individual subject basis.

An aliquot of urine for storage will be collected for potential future analysis for any subject that meets renal stopping and follow-up criteria at any time during the study. Additionally, at Visit 85 (week 68), Visit 117 (week 104) and yearly thereafter or early withdrawal, an aliquot of urine will be obtained and frozen for each subject to allow for storage and potential future analysis of emerging renal biomarkers

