All subjects will have an 8 week interruption to drug administration, following completion of Visit 85 (or as soon as Amendment 7 is approved after Visit 85). During the 8 weeks off drug, subjects will be asked to return for Visit 89 where safety parameters and efficacy measures will be made. Additional visits can be arranged depending on the current clinical status of the

subject and the clinical judgement of the investigator. Subjects will then re-start study administration according to a dosing regimen of;

- Subjects will receive one dose of 6 mg/kg PRO051 per week x 8 weeks if their body weight is  $\leq 50$  kg. This will be followed by 4 weeks off drug. This will continue in a cyclical manner.
- If a subjects body weight  $>50$  kg, he will receive one maximal dose of 300 mg PRO051 per week x 8 weeks This will be followed by 4 weeks off drug. This will continue in a cyclical manner.

Based on PK/PD modelling this regimen is predicted to result in an overall 12-week exposure that is somewhat lower than the continuous dosing regimen. The dystrophin levels are predicted to fluctuate between about 70% of the current level at the end of the off drug period, to about 80% at the end of the 8 weeks on drug. Although a compromise in efficacy is not anticipated, the impact on response will be closely monitored and if a perceived continuous decline in efficacy is observed, the investigator will discuss the potential benefit for an individual subject to return to continuous weekly dosing at 6mg/kg PRO051 with the Medical Monitor where the safety and tolerability is acceptable. The intermittent dosing regimen may, however, help to minimize organ burden from accumulation of this compound in organs, such as liver and kidney by allowing organs to washout during the off-treatment period. The overall risk benefit profile will be regularly assessed. Any change from intermittent dosing to continuous weekly dosing will be implemented at the start of a 12 week cycle.

The treatment with PRO051 beyond the study period should comply with the following conditions:

- Subject benefits from the PRO051 treatment
- Safety and effect assessments are performed as described in Appendix 2: Table 6, Table 7, Table 8 and Table 9.
- Maximum treatment period is until (whichever comes first):
  - the start of a next trial with PRO051 for which the subject is eligible, or
  - is exposed to safety risks outweighing potential benefits, or

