### **5.6.5.2      Thrombocyte Count**

Thrombocyte count will be performed on a two weekly basis during the treatment part of each 12 week cycle, and the following monitoring and discontinuation criteria apply:

- If thrombocytes are below the lower level of the normal range, thrombocytes will be checked prior to the next scheduled dose of study medication. Study medication will only be administered if thrombocytes are  $>75 \times 10^9/L$ ;
- If thrombocytes are still  $<75 \times 10^9/L$ , they will be checked on alternate days until they reach  $>100 \times 10^9/L$ ;
- If thrombocytes are  $<75 \times 10^9/L$ , study medication will be stopped and will only be considered for re-challenge should a clear alternative (non-drug related) cause be found after discussion between the Sponsor and Investigator;
- If the thrombocyte count has fallen  $>25\%$  from the previous count and is  $<100 \times 10^9/L$  then study medication should not be administered until thrombocytes return to  $>100 \times 10^9/L$ ;
- Investigators should be alert to trends for a consistent decrease in thrombocytes over two or more visits that may not meet the above criteria.

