#### **6.3.2 During treatment beyond period**

The study medication will be delivered as solution for subcutaneous injection in vials containing 1 ml of 200 mg/ml of GSK2402968 (formerly PRO051). Before drawing the solution, the vials need to be at ambient temperature and subsequently shaken manually for at least 10 seconds. Medication will be injected by qualified personnel in the abdominal subcutis. As there is the potential for injection site reactions with repeated study drug administration, it is strongly recommended to try and minimize any skin reactions by rotation of the injection site. Detailed instructions for the rotation of injection sites are provided in the Investigator Manual. The drug product should be administered within 4 hours after preparation. If the Investigator is confident that there are no medical concerns, subjects may receive some injections at home administered by a qualified person approved by the Investigator. All subjects must continue to attend the investigative site at least once a month

for each full assessment visit and all efficacy assessments must be done in the clinic. If the qualified person administering the injections has any concerns on subject wellbeing, the Investigator should be contacted by the qualified person to discuss and the subject may need to attend the clinic for the following injection.

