| Study medication administration  | x                                                                                    | x     | x     | x     |       |       |       |       | x     | x     | x     | x     | x     | x     | x     | x     |       |       |       |       | x     | x     | x     | x     |                                              |
| Weekly dosing option            | x                                                                                    | x     | x     | x     | x     | x     | x     | x     | x     | x     | x     | x     | x     | x     | x     | x     | x     | x     | x     | x     | x     | x     | x     | x     |                                              |
| Physical examination                         |                                                                                      |       |       |       |       |       |       |       |       |       |       | x     |       |       |       |       |       |       |       |       |       |       |       | x     | x                                            |
| Vital signs                      |                                                                                      |       |       |       |       |       |       |       |       |       |       | x     |       |       |       |       |       |       |       |       |       |       |       | x     | x                                            |
| Weight, height                               |                                                                                      |       |       |       |       |       |       |       |       |       |       | x     |       |       |       |       |       |       |       |       |       |       |       | x     |                                              |
| ECG                                          |                                                                                      |       |       | x     |       |       |       |       | x     |       |       | x     |       |       |       | x     |       |       |       |       | x     |       |       | x     | x                                            |

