| DEXA scan                        | x                                                                                    | x     | x     | x     | x     | x     | x     | x     | x     | x     | x     | x     | x     | x     | x     | x     | x     | x     | x     | x     | x     | x     | x     | x     | x                                            |
| Adverse events                  | x                                                                                    | x     | x     | x     | x     | x     | x     | x     | x     | x     | x     | x     | x     | x     | x     | x     | x     | x     | x     | x     | x     | x     | x     | x     | x                                            |
| Concomitant medication          | x                                                                                    | x     | x     | x     | x     | x     | x     | x     | x     | x     | x     | x     | x     | x     | x     | x     | x     | x     | x     | x     | x     | x     | x     | x     | x                                            |

1. Other assessments to be performed prior to study medication administration unless specified otherwise

2. Vital signs include temperature, blood pressure, pulse and respiratory rate
3. Parameters will be derived from M-mode measurements and include left ventricular ejection fraction, fractional shortening, left ventricular posterior wall thickness, left ventricular septum wall thickness, left ventricular end systolic diameter, left ventricular end diastolic diameter, and left ventricular ejection fraction modified Simpson's
4. Collect a first morning urine specimen
5. Via finger prick
6. Timed tests consist of: 10-meter walk/run, rising from floor, stair climb
7. Parameters include FVC, FEV1, mouth pressure inhale, mouth pressure exhale, peak flow, peak cough flow
8. A DEXA scan may be performed at any visit, if deemed clinically necessary by the Investigator (i.e. rapid weight gain)
9. Prior to study medication administration
10. Adverse events to be obtained by weekly telephone call to parents by investigator / study nurse during off drug periods
11. Concomitant medication to be obtained by weekly telephone call to parents by investigator / study nurse during off drug periods
12. Weekly dosing: Decision to return to weekly dosing PRO051 will be made after full discussion between principal investigator and medical monitor

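### Tables 12–14 allow weekly dosing at every visit but leave 5-week intervals with no urine protein or platelet test marked, against the two-weekly on-treatment rule

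*Protocol*

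**What the plan says.** Two sections of the protocol set the on-treatment frequency. Section 5.6.8.2 states that urinalysis "will be conducted every 2 weeks during the treatment part of each 12 week cycle". Section 5.6.5.2 states: "Thrombocyte count will be performed on a two weekly basis during the treatment part of each 12 week cycle".

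The treatment-beyond-study text of section 3.3 puts boys on 8 weeks of drug and 4 weeks off. One stated reason is that this may "help to minimize organ burden from accumulation of this compound in organs, such as liver and kidney". The same text lets an individual boy return to continuous weekly dosing if efficacy seems to decline and tolerability is acceptable. It fixes the timing: "Any change from intermittent dosing to continuous weekly dosing will be implemented at the start of a 12 week cycle".

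Tables 12, 13 and 14 in Appendix 2 each carry a row, "Weekly dosing option", marked at all 24 visits. Its footnote 12 concerns only who decides: "Weekly dosing: Decision to return to weekly dosing PRO051 will be made after full discussion between principal investigator and medical monitor". The note above each table waives laboratory visits during the 4-week treatment break.

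On attendance, section 6.3.2 says: "All subjects must continue to attend the investigative site at least once a month" and continues "for each full assessment visit and all efficacy assessments must be done in the clinic".

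**The concern.** A boy dosed in all 12 weeks of a cycle has no off-drug part, so the two-weekly rule applies to him throughout. The tables mark his doses but not the tests that go with them in the four former off-drug weeks.

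Section 5.6.5.1 calls hepatic, renal and thrombocyte monitoring of paramount importance, and the stopping rules need a sample to act on. A platelet count below normal already forces a recheck before the next dose (5.6.5.2), so the platelet exposure is in boys whose last count was normal. For urine, a moderately raised protein value stops the drug only when a second consecutive sample confirms it (5.6.5.9). If the first such value falls at visit 161, the next marked sample is at visit 166, after five more doses.

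These boys have also lost the washout weeks. They receive 12 doses per cycle instead of 8, with no test added.

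**Working it through.** **Inputs.** The marks in Tables 12–14, with visits one week apart. Platelets are measured by the finger-prick row and by the safety haematology panel, which includes thrombocytes (Appendix 3). Footnote 1 places tests before that day's dose.

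**1. Marks.** In Table 12, urine is marked at visits 159, 161, 166, 167, 169, 171, 173, 178, 179 and 181. Finger prick (159, 167, 171, 179) plus haematology (161, 166, 169, 173, 178, 181) gives the same ten visits for platelets. Tables 13 and 14 repeat the pattern, so there are 3 × 10 = 30 marks of each kind.

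**2. Intermittent regimen: the rule is met.** All on-treatment intervals are 1 or 2 weeks, and at most two doses fall between tests.

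**3. Weekly option: the rule is not met.** For both tests the intervals longer than 2 weeks are 161–166, 173–178, 185–190, 197–202, 209–214 and 221–226, each of 5 weeks. In the first, doses at 161, 162, 163, 164 and 165 fall between two tests.

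**4. How many one boy meets.** Intermittent cycles start at visit 94 and every 12 visits after: … 154, 166, 178, 190, 202, 214, 226. A switch is made only at a cycle start.

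| Switch at visit | 5-week intervals met |
|---|---|
| 154 or earlier | 6 |
| 166 | 5 |
| 178 | 4 |
| 190 | 3 |
| 202 | 2 |
| 214 | 1 |
| 226 | 0 |

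Table 11 (visits 134–157) has no weekly-option row, so five is the better-supported maximum. Six requires a switch by visit 154, which would fit Table 12 marking weekly dosing at 158–165.

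**5. Net shortfall.** Two-weekly testing over 72 weeks needs 72 / 2 = 36 tests of each kind. The tables give 30. The difference is 6 over six cycles, or one per cycle (5 marks instead of 6).

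**6. Full panel.** Biochemistry and haematology marks at 161, 166, 169, 173, 178 give intervals of 5, 3, 4 and 5 weeks. Once per cycle this exceeds the month in 6.3.2.

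**7. Comparison.** Table 8 covers the last period of continuous weekly dosing before the intermittent regimen. From visit 65 to 85 it marks urine and platelets every 2 weeks.

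**The case against.** The strongest reply is that the text already demands these tests. Section 5.6.5.2 sets the platelet frequency without pointing to the tables, 5.6.8.2 does the same for urinalysis, and 6.3.2 requires monthly attendance. The break waiver cannot apply to a boy without a break. A site would have to follow the table against all three to miss the tests. This stands, and it limits the point to a table that conflicts with its rule. It does not remove the conflict: 5.6.5.9 and 5.6.5.1 send sites to Tables 6–14 for the exact time points of urinalysis and of the haematology panel.

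A second reply is that 5.6.5.9 orders a 4-weekly urine sample after visit 61. Counted literally, that falls at visits 165, 177, 189, 201, 213 and 225, one inside each interval. But this sample is for alpha-1-microglobulin, KIM-1 and cystatin C. It replaces neither urine protein nor platelets, is not two-weekly, and is not marked in these intervals either.

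Third, weekly dosing is an individual exception agreed with the medical monitor. That is true, and boys on the intermittent regimen are unaffected.

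A reader might infer that each interval lacks two tests, so that 12 of each kind are missing. That counts the marks needed to close the intervals while keeping those at 166-type visits. Against a two-weekly rule the net deficit is 6.

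**Conclusion.** The point holds as a conflict between tables and text that should be corrected. On the weekly option, Tables 12–14 leave five 5-week intervals (six only with a switch by visit 154) without a urine protein or platelet mark, where the rule is 2 weeks. Five doses fall between tests. The defect is chiefly spacing, with a net shortfall of about one test of each kind per cycle.

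A reader might go further and infer that the plan leaves these boys unmonitored. The documents do not support that, because the two-weekly rule in the text still binds.

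The conclusion rests on two assumptions. One is that, for a boy dosed all 12 weeks, the whole cycle is its treatment part; on any other reading the protocol gives him no two-weekly rule at all. The other is that no separate test schedule for weekly dosing stands in the opening of the treatment-beyond-study subsection, which is missing from the copy reviewed.

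**What to change.** In Tables 12–14, for boys on the weekly option only, add urine and thrombocyte marks at visits 163, 165, 175, 177, 187, 189, 199, 201, 211, 213, 223 and 225. The sequence 161, 163, 165, 166, 167, 169 then has intervals of 2, 2, 1, 1 and 2 weeks, so none exceeds 2. State in footnote 12 that the treatment-break waiver does not apply to these boys.

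This gives 30 + 12 = 42 tests of each kind, more than the 36 the rule needs. The 167-type tests may be dropped only if spacing stays at 2 weeks or less. With neighbours at 166 and 169 it would be 3 weeks, so on the present marks they must stay. The added marks also leave the full panel at 5 weeks once per cycle. If the sponsor moved the 166-type panel and urine to 165 for these boys, the panel would run 4-weekly (161, 165, 169, 173, 177) and two-weekly testing would need only 36 tests.

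The cost is table marks, one footnote sentence, and at most 12 extra finger pricks and 12 extra morning urines per weekly-dosed boy (10 of each if he switches at visit 166). That is a real burden for children, but the text already asks for two-weekly tests.

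A minor wording point can be settled in the same amendment. Section 5.6.8.2 ties the 24-hour urine to consecutive weekly samples although sampling is two-weekly. Section 5.6.5.9 does require two consecutive samples for two of its triggers, but not weekly ones, and none for serum cystatin C. Section 5.6.8.2 should simply refer to the 5.6.5.9 triggers as they stand.

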#### **5.6.5.9      Urinalysis**

A first morning urine specimen is collected at selected visits (refer to Tables 6 - 14 in Appendix 2 for the exact time points) in order to assess the urinalysis parameters as described in Appendix 3.

At visit 13, 25, 37, 49, 61 and 4 weekly thereafter an additional first morning sample of urine is collected for alpha-1-microglobulin, KIM-1 and cystatin C assessment.

- If during treatment any of the following occur, study drug must be stopped and a 24-hour urinalysis performed as soon as possible but at the latest by the next scheduled visit: urinary protein concentration  $\geq 0.2$  g/L and  $< 0.45$ g/L on two consecutive samples;
  - NOTE: if urinary protein concentration is  $\geq 0.45$ g/L on urinalysis, stop study drug and repeat protein analysis. If the repeat urinary protein value is  $\geq 0.2$ g/L, continue to withhold study drug and perform a 24 hour urinalysis. If the repeat urinary protein is  $< 0.2$ g/L, study drug may be restarted.
- protein/creatinine ratio in the morning sample is  $> 0.5$  on two consecutive samples;
- serum concentration of cystatin C is above the normal range and 50% above the baseline value.

24-hour urinalysis to include creatinine concentrations for creatinine clearance assessment, total protein and protein electrophoresis.

If the results of the 24-hour urinalysis triggered by any of the above do not meet criteria defined in section 5.6.8.2, study drug may be restarted.

The urine samples will be collected and processed according to standard hospital procedures and assessed by the local laboratory of the participating sites.

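### Protocol 5.6.8.2 restates the 24-hour urinalysis trigger wrongly: it asks for two consecutive weekly samples, which 5.6.5.9 does not require and the two-weekly urine schedule seldom supplies

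*Protocol*

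**What the plan says.** Two sections govern the 24-hour urinalysis in the treatment beyond the study period.

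Section 5.6.5.9 (Urinalysis) lists the screening findings on which "study drug must be stopped and a 24-hour urinalysis performed as soon as possible but at the latest by the next scheduled visit". They are:

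- urinary protein from 0.2 to below 0.45 g/L on two consecutive samples;
- protein/creatinine ratio above 0.5 in the morning sample on two consecutive samples;
- "serum concentration of cystatin C is above the normal range and 50% above the baseline value", with no second sample asked for.

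A NOTE covers a single urinary protein of 0.45 g/L or more: stop drug and repeat. If the repeat is 0.2 g/L or more, the instruction is to "continue to withhold study drug and perform a 24 hour urinalysis". None of these rules states an interval between samples. If the 24-hour results "do not meet criteria defined in section 5.6.8.2, study drug may be restarted".

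Section 5.6.8.2 (Renal Toxicity) first says that urinalysis "will be conducted every 2 weeks during the treatment part of each 12 week cycle". It then says: "24-hour urinalysis will be conducted if any of the criteria described in Section 5.6.5.9 are met on two consecutive weekly samples". Its stopping criteria follow. Two of them are read from the 24-hour collection: "Proteinuria in 24-hour urine sample is either" above 300 mg/day or 8 mg/m²/h, and "Albumin excretion in 24-hour urine sample is" above 50 mg/day. The third, casts or erythrocytes, uses a fresh spot urine.

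**The concern.** Section 5.6.8.2 presents itself as a restatement of the 5.6.5.9 trigger but changes it in two ways. It adds weekly spacing, one sentence after fixing a two-weekly schedule. By applying the two-sample condition to every criterion, it also asks, read literally, for a second sample where the cystatin C rule needs one value, and it does not fit the NOTE, whose repeat has its own lower limit and no interval.

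The 24-hour collection supplies two of the three renal stopping criteria and decides whether held drug may be restarted. A site that holds drug under 5.6.5.9 but takes the condition for the test from the section headed Renal Toxicity could wait for a weekly pair that is not soon due. The boy would then be off drug without the result that separates a restart from a confirmed renal stop. Section 5.6.5.1 singles out renal monitoring because the drug accumulates in the kidney, so this trigger should read the same wherever it appears.

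**Working it through.** **Inputs.** The urine protein/creatinine and serum cystatin C rows of Appendix 2, Tables 9 to 14. Consecutive visit numbers are one week apart. Cyclic dosing starts at visit 94 (Table 9 shows no dose at visits 86 to 93) and the tables end at visit 229.

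**Urine protein/creatinine visits.** First cycle: 95, 97, 99, 101. Each later cycle, with first visit *s* = 106, 118, ..., 226: *s*, *s*+1, *s*+3, *s*+5, *s*+7. The last cycle is cut off at 229, so it gives 226, 227 and 229.

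- Samples: 4 + 10 × 5 + 3 = 57, hence 56 gaps.
- One-week gaps: one per cycle from the second on (106–107, 118–119, ..., 226–227) = 11.
- Two-week gaps: 3 in the first cycle + 3 in each of the next 10 + 1 in the last = 34.
- Five-week gaps across the drug break: 11.
- Check: 11 + 34 + 11 = 56.

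**Share of pairs that can be weekly.**

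| Pairs | Weekly | Total | Share |
|---|---|---|---|
| Within a treatment cycle | 11 | 45 | 24% |
| All, including those across the break | 11 | 56 | 20% |

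The other 34 of 45 within-cycle pairs (76%) are two weeks apart. The tables therefore bear out the two-weekly frequency in 5.6.8.2, apart from the extra sample at the start of each cycle from the second on. The first cycle has no weekly pair. Visit 93 also has a urine sample, but it is off drug and is left out. Counting it would add one two-week pair (11 of 46 within cycle, 11 of 57 overall) and change nothing of substance. Table 9 gives a visit window of ±1 day and Tables 10 to 14 a dosing window of ±1 day; neither turns a two-week gap into one week.

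**Serum cystatin C visits.** 97, 109, 113, 118, 121, 125, 130, 133, and so on to 229: 32 samples and 31 gaps (10 of 3 weeks, 10 of 4, 10 of 5, one of 12). The shortest is 3 weeks, so no scheduled pair is weekly.

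**Distance to the next weekly pair.** Take each of the 34 two-week pairs and count weeks from its second sample to the end of the next scheduled weekly pair. For example, visit 109 to 119 is 10, 111 to 119 is 8, and 113 to 119 is 6. The result is 10 weeks for 11 pairs, 8 weeks for 11, 6 weeks for 11, and none left on the printed schedule for one (ending at visit 229). Section 5.6.5.9 wants the test by the next scheduled visit.

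**With the weekly condition removed.** All 56 successive urine pairs, and every single scheduled cystatin C value, could operate the trigger as 5.6.5.9 describes it.

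**The case against.** The strongest reply is that both sections can be obeyed together. Section 5.6.8.2 says the test is done *if* the weekly condition is met, not *only if*. Section 5.6.5.9 orders the test separately, in the same sentence as the drug hold and with a deadline, and its restart rule refers to a collection triggered by its own list. A site would have to follow half of that sentence and ignore the other half. Even then the boy is off drug. The phrase also follows a sentence on urinalysis, so weekly samples is naturally read as urine, which makes the spacing of a serum marker a strictly literal point.

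Much of this stands. The hold is stated only in 5.6.5.9 and nothing in 5.6.8.2 weakens it. A reader might infer that under 5.6.8.2 a boy with raised screening values would stay on drug; the text does not support that, because 5.6.8.2 does not address the screening hold. A reader might also take the 6, 8 or 10 weeks as an expected delay. They are not: they arise only if a site takes the test trigger from 5.6.8.2 and takes no unscheduled sample.

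What the reply does not remove is that 5.6.8.2 cites the 5.6.5.9 criteria and then states a different condition for them, next to a schedule that mostly cannot meet it. That the sentences can be reconciled by careful reading does not make the restated trigger correct.

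**Conclusion.** Section 5.6.8.2 is wrong as written on the trigger for the 24-hour urinalysis. Its weekly condition can be met on schedule by 11 of 45 within-cycle urine pairs (24%), or 11 of 56 overall (20%), and by no pair of serum cystatin C samples. The condition appears nowhere in 5.6.5.9.

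The consequence is limited. It touches the timing of the 24-hour test only, and only at a site that works from 5.6.8.2. Such a site could delay the result that decides between restart and a confirmed renal stop. The drug hold, the order for the test in 5.6.5.9, the spot-urine criterion and every threshold are unaffected.

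The figures rest on reading the Appendix 2 marks by column and on one week per visit number. They are counts on the schedule, not rates of renal events or forecasts of delay. The change should be made because the sentence states a safety trigger and the correction is simple.

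**What to change.** In 5.6.8.2, end the sentence on the 24-hour urinalysis by saying that the criteria *are met as specified in Section 5.6.5.9*, in place of the closing condition on two consecutive weekly samples. Leave 5.6.5.9 as it is, including the NOTE for protein of 0.45 g/L or more and the single-value cystatin C rule. Leave all limits, hold and restart rules unchanged.

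The cost is one phrase. It needs no new visit, sample or assay.
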